### Explorative outcome measures

The following explorative outcome measures are collected for research purposes to compare patient groups and treatment. Time points for data collection are depicted in Fig. 3.Long-term DASH score at 2 years and 5 yearsLong-term EQ-5D-5L score at 2 years and 5 yearsRadiological measurements [47]Gross instability of the fracture site [17]NonunionTime of return to workLevel of activity by the UCLA activity score [48]

### Other outcome measures

Any ancillary outcome measure or analysis will be reported.

## Statistical analysis plan

### Hypothesis

The null hypothesis is:The DASH score at 52 weeks after surgical treatment is not superior to non-surgical treatment with the option of early crossover surgery in patients with humeral shaft fractures

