### Trial design

A pragmatic multicenter, randomized, controlled, outcome assessor-blinded, clinical superiority trials. The steering committee which consist of trauma- and shoulder-elbow surgeons have assessed the pragmatic design using PRECIS-2 [33] which yielded 37 points out of the possible 45 points (Fig. 1). An explanation for each domain score is provided in Appendix 1. This study furthermore collaborates with the NORCRIN Work Package 13 network.

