### Interim analyses

We will carry out two interim analyses after trial completion of 25% and 50% of the planned number of included patients, separately for the two age groups. We will use the O’Brien-Fleming rule [37] for determining appropriate significance levels for each analysis, which is determined by time of hypothesis testing (*n*=3) and the overall significance level of *α*=0.05. Under these assumptions, the significance levels are 0.0006 for the first interim analysis, 0.0151 for the second interim analysis, and 0.0471 for the final analysis. Interim analyses will be carried out for both the primary endpoint (DASH) and for serious complications (iatrogenic nerve injury, deep infection, major adverse cardiac events (MACE), other major adverse events, and death) and will be conducted by one-sided tests to determine if the improvement in DASH is significantly above 25 points, respectively if the complication rate is at least 20% higher.

A Data Monitoring Committee (DMC) has been organized to monitor and evaluate the data from the interim analyses. The DMC consists of five independent members including the patient representative (PR), two orthopedic researchers, an orthopedic surgeon, and a nurse.

In the event of one group having zero complications, the significance level cannot be computed by a cChi-square test, and the DMC will have to assess the data due to a statistical variation.

In the event of a patient sustaining several complications, the most severe complication will follow the patient. The complications are ranked in a hierarchy model describing the severity and are ranked from most severe to least severe: death, MACE, deep infection with debridement, other reasons for hospitalization, and iatrogenic nerve injury.

The interim analyses will be conducted by a biostatistician, blinded to the treatment allocation. Data will then be presented to the DMC, in means and proportions and be accompanied with confidence intervals. The DMC will have access to the data unblinded, and if at least one of those two conditions is fulfilled or a statistical variation has occurred at an interim analysis the DMC will be asked to investigate the results in detail and present their recommendation to continue or stop the trial. In the event of disagreement with a split decision (one or more casts a blank vote), the steering committee will be involved in discussing the stopping of the trial.

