### Sample size

The two groups (SHAFT-Y and SHAFT-E) require individual sample size calculations. Two standard deviations (SDs) were obtained from the data of the FISH trial [13] and were separated in age groups of 18–64 years and 65 years and above. By the distribution-based approach, one half a SD corresponds to the minimal important change (MIC) [49]. The calculations are powered to detect a MIC of 7 points in the young and 10 points in the elderly group in DASH, respectively. Two independent means sample size calculations were performed. For SHAFT-Y the following data were included: mean difference = 7.0, SD= 14.91, *α*= 0.05, and power= 0.8. For SHAFT-E the following data were included: mean difference= 10.0, SD= 18.59, α= 0.05 and power= 0.8. Based on the preceding assumptions and including an attrition of 15%, the total sample size is estimated to 163 patients for SHAFT-Y and 124 patients for SHAFT-E.

The FISH trial [13] experienced 5% attrition, since more sites are involved in SHAFT the attrition is set to 15%.

The steering committee can decide to pool data from both RCTs (SHAFT-Y, SHAFT-E) if recruitment is prolonged.

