### Primary analysis

Descriptive statistics will be used to report demographic data. Demographic data and outcome measures will be tested visually and statistically (i.e., Shapiro Wilks test). Numeric variables will be summarized by means, standard deviations, and 95% confidence intervals (95% CI). Median and interquartile ranges will be used when normal distribution is not met. Categorical variables will be summarized by frequency and proportion. For group comparison with numerical data, a student’s t-test will be used if data is normally distributed, otherwise, a non-parametric test will be used. For categorical data, a chi-square test will be used for group comparison. An intention-to-treat (ITT) analysis of the primary outcome will be conducted by univariable linear regression, including all patients that do not meet the withdrawal criteria, and will be conducted to minimize bias within results. A sensitivity analysis will test the effects of non-adherence to protocol by conducting a per-protocol analysis and includes only patients who comply with the protocol. For missing data points in an outcome measure, a multiple imputation analysis using predictive covariates (age, sex, smoking, alcohol, UCLA activity, ASA grade) [50–52] will be conducted to deal with nonresponse bias. For comparison, we will carry out a sensitivity analysis excluding all the missing values.

Data will be considered statistically significant if *p* values < 0.0471.

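### The null is directional and the interim tests are one-sided, but the sample size and alpha levels are two-sided and the final test names no side

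*Protocol article*

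**What the plan says.** All references are to the protocol article.

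- **Trial design** describes "randomized, controlled, outcome assessor-blinded, clinical superiority trials" and names no side.
- **Hypothesis** (under Statistical analysis plan) gives the null: "The DASH score at 52 weeks after surgical treatment is not superior to non-surgical treatment". The only alternative to it is that surgery is better.
- **Interim analyses** sets up three tests under the O'Brien-Fleming rule with "the overall significance level of *α*=0.05", so that "the significance levels are 0.0006 for the first interim analysis, 0.0151 for the second interim analysis, and 0.0471 for the final analysis". The interim tests "will be conducted by one-sided tests to determine if the improvement in DASH is significantly above 25 points".
- **Sample size** uses, for SHAFT-Y, "mean difference = 7.0, SD= 14.91, *α*= 0.05, and power= 0.8". SHAFT-E has a difference of 10.0 and an SD of 18.59 with the same alpha and power. Neither calculation names a side. With 15% attrition the totals are 163 and 124.
- **Primary analysis** tests the primary outcome by univariable linear regression and closes with: "Data will be considered statistically significant if *p* values < 0.0471". Again no side is named.

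The term two-sided appears nowhere in the article.

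**The concern.** A directional null tested one-sided and a null of no difference tested two-sided are different decision rules, even at the same nominal level. The two sections that show a direction (Hypothesis and Interim analyses) point to the first. The figures that fix the design (sample size and alpha levels) point to the second. The final threshold of 0.0471 is the last member of the series whose earlier members are attached to one-sided tests, and it carries no side of its own.

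Two things are at stake. A borderline result in favour of surgery could be called significant or not, according to which section is followed. And a clear result in favour of non-surgical treatment has no formal place, because it cannot reject the null as written. Such a result is conceivable: Background and rationale lists several surgical complications, and the comparator includes early crossover surgery meant to shorten failed courses.

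**Working it through.** **1. Which side reproduces the stated totals?** Inputs are from Sample size; 1:1 allocation is from Randomization. For two independent means, total N = 4 × (z_alpha + 0.8416)² × (SD/difference)².

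| | SHAFT-Y (7.0; 14.91) | SHAFT-E (10.0; 18.59) |
|---|---|---|
| Two-sided 0.05, z = 1.960 | 142.4 | 108.5 |
| Truncated, × 1.15 | 142 × 1.15 = 163.3 | 108 × 1.15 = 124.2 |
| One-sided 0.05, z = 1.645 | 112.2 | 85.5 |
| Unrounded, × 1.15 | 129.0 | 98.3 |
| One-sided, rounded up per arm, × 1.15 | 132 | 99 |
| One-sided, rounded up per arm, ÷ 0.85 | 135 | 102 |
| **Stated** | **163** | **124** |

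The two-sided calculation gives the stated totals. No one-sided variant comes near them.

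**2. Which side fits the alpha levels?** With three equally spaced tests, O'Brien-Fleming critical values follow z_k = z_3 × √(3/k).

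| Level | z if two-sided | Shape from 1.985 | z if one-sided | Shape from 1.674 |
|---|---|---|---|---|
| 0.0006 | 3.43 | 1.985 × √3 = 3.44 | 3.24 | 1.674 × √3 = 2.90 |
| 0.0151 | 2.43 | 1.985 × √1.5 = 2.43 | 2.17 | 1.674 × √1.5 = 2.05 |
| 0.0471 | 1.985 | 1.985 | 1.674 | 1.674 |

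Only the two-sided reading has the right shape. The shape is the evidence here, not the overall error. For tests against zero at equal spacing, simulation gives about 0.052 two-sided and 0.051 one-sided, so the overall error does not separate the readings.

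**3. What differs at the final analysis?** With 15% loss, 0.85 × 163 = 138.55 and 0.85 × 124 = 105.4 patients are analysed. SE = SD × √(4/N).

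- SHAFT-Y: 14.91 × √(4/138.55) = 2.533
- SHAFT-E: 18.59 × √(4/105.4) = 3.622

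| At p < 0.0471 | One-sided (z = 1.674) | Two-sided (z = 1.985) |
|---|---|---|
| Smallest significant difference, SHAFT-Y | 1.674 × 2.533 = 4.24 | 1.985 × 2.533 = 5.03 |
| Smallest significant difference, SHAFT-E | 1.674 × 3.622 = 6.06 | 1.985 × 3.622 = 7.19 |
| Power at 7.0, SHAFT-Y | 86.2% | 78.2% |
| Power at 10.0, SHAFT-E | 86.2% | 78.1% |
| Nominal chance of a false claim for surgery at this test | 4.7% | 0.0471/2 = 2.4% |

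**4. Does the side of the interim DASH test matter?** Take the 25 points as a between-arm difference (an assumption) and the interims at 25% and 50% of the analysed numbers. The SE is then 2 × and √2 × the final SE.

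- SHAFT-Y at 25%: SE 5.07; crossing needs 25 + 3.24 × 5.07 = 41.4 points, about 8 SEs from zero.
- SHAFT-Y at 50%: SE 3.58; 25 + 2.17 × 3.58 = 32.8 points, about 9 SEs.
- SHAFT-E at 25%: SE 7.24; 25 + 3.24 × 7.24 = 48.5 points, about 6.7 SEs.
- SHAFT-E at 50%: SE 5.12; 25 + 2.17 × 5.12 = 36.1 points, about 7 SEs.

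If the arms do not differ, the interim DASH test almost never crosses, whichever side is used.

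**The case against.** The strongest reply is that there is only one live rule. No section prescribes a one-sided final test; that word is used only for the interims. Regression p-values are two-sided by default, the reported intervals are 95% intervals, and the sample size and alpha levels agree with both. A null of not superior is a common loose wording in a trial labelled superiority, where a two-sided test is read in the favourable direction. The side of a p-value is also something an article may leave to a separate analysis plan.

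Much of this stands. The two-sided reading is the likelier one, and an unstated side alone would not be a finding. What remains is what the article does state: a null with one direction, and one-sided tests placed in a series of two-sided levels. These conflict with the design figures and are not missing detail.

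Three stronger inferences are tempting, and the documents do not support them:

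- *The trial will test one-sided at 0.0471 and so double its false-positive rate for surgery.* That rule is assembled from separate sections and is written in none.
- *The one-sided interims inflate the false-positive rate for DASH.* They test against a 25-point shift and prompt a review and recommendation by the monitoring committee; step 4 shows that the effect is negligible. Their side does not by itself set the side of the final test.
- *The Primary analysis section already calls a result favouring non-surgical treatment significant.* That holds only if its threshold is read as two-sided.

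**Conclusion.** The inconsistency is real and limited in size. The design figures are two-sided, while the formal hypothesis and the interim tests are directional. If the one-sided reading were taken up, results of about 4.2 to 5.0 points in SHAFT-Y and 6.1 to 7.2 points in SHAFT-E would change from not significant to significant. Independently of borderline results, the null as written gives no formal conclusion if non-surgical treatment proves better.

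This rests on three assumptions: the two-sided basis of the sample size is inferred from reproducing 163 and 124, since the article does not state it; the planning SDs hold; and 15% of patients are lost. The way attrition was added, the spacing of the looks and the choice of 25 points are separate matters that this point does not rely on.

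**What to change.** - **Hypothesis:** restate the null as no difference in mean 52-week DASH between surgical treatment and non-surgical treatment with early crossover allowed. Superiority of either arm can then be concluded.
- **Sample size:** state that alpha 0.05 is two-sided.
- **Primary analysis:** state that the final test is two-sided at the stated level.
- **Interim analyses:** reconcile the side of the tests with the two-sided levels. Either make the tests two-sided, or use half the nominal level for any DASH test kept one-sided. For DASH this is for coherence only.

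The cost is a wording amendment, best made before any unblinded comparison. Neither the sample size nor the final level of 0.0471 changes on this account, because the stated totals already fit a two-sided test.

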### Sample size

The two groups (SHAFT-Y and SHAFT-E) require individual sample size calculations. Two standard deviations (SDs) were obtained from the data of the FISH trial [13] and were separated in age groups of 18–64 years and 65 years and above. By the distribution-based approach, one half a SD corresponds to the minimal important change (MIC) [49]. The calculations are powered to detect a MIC of 7 points in the young and 10 points in the elderly group in DASH, respectively. Two independent means sample size calculations were performed. For SHAFT-Y the following data were included: mean difference = 7.0, SD= 14.91, *α*= 0.05, and power= 0.8. For SHAFT-E the following data were included: mean difference= 10.0, SD= 18.59, α= 0.05 and power= 0.8. Based on the preceding assumptions and including an attrition of 15%, the total sample size is estimated to 163 patients for SHAFT-Y and 124 patients for SHAFT-E.

The FISH trial [13] experienced 5% attrition, since more sites are involved in SHAFT the attrition is set to 15%.

The steering committee can decide to pool data from both RCTs (SHAFT-Y, SHAFT-E) if recruitment is prolonged.

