### Material

Two hundred eighty-seven patients (*n*=163 for SHAFT-Y, *n*=124 for SHAFT-E) with a humeral shaft fracture will be equally randomized to surgical treatment or non-surgical treatment in each group. The overall trial flow and timeline of data collection is outlined in Figs. 2a, b and 3.

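### At the plan's own 15% attrition and final level of 0.0471, the stated sample sizes give about 77–78% power, not 80%

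*Protocol article*

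**What the plan says.** The Sample size section gives separate calculations for the two age groups. It states that "Two independent means sample size calculations were performed". For SHAFT-Y the inputs are "mean difference = 7.0, SD= 14.91", with alpha 0.05 and power 0.8. For SHAFT-E they are "mean difference= 10.0, SD= 18.59, α= 0.05 and power= 0.8". The result is given as "including an attrition of 15%, the total sample size is estimated to 163 patients for SHAFT-Y and 124 patients for SHAFT-E". The section adds that the source trial lost 5% and that 15% was chosen because SHAFT has more sites. It prints neither the formula for the attrition allowance nor the sidedness of the test.

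The Interim analyses section assigns O'Brien-Fleming levels of 0.0006, 0.0151 and 0.0471 to two interim looks and the final analysis. The Primary analysis section applies the last of these: "Data will be considered statistically significant if *p* values < 0.0471". The same section makes univariable linear regression the primary model. The Material section carries the two totals forward as "Two hundred eighty-seven patients".

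**The concern.** Two steps in the sample size calculation do not fit the rest of the plan.

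- **Attrition.** If a fraction of 0.15 is lost, the number to recruit is the required number divided by 0.85. Multiplying by 1.15 recruits too few, because the 15% is then lost from the larger total.
- **Significance level.** The trials are sized at 0.05, but the final test is stricter because of the interim looks. The Sample size section makes no allowance for this.

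Both steps act in the same direction. At stake is the accuracy of a headline design statement, 80% power with 15% attrition, in both trials. The validity of the test, its type I error and the treatment estimate are not affected.

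**Working it through.** **Inputs.** From Sample size: difference 7.0 and SD 14.91 (Y); difference 10.0 and SD 18.59 (E); alpha 0.05; power 0.80; attrition 15%; totals 163 and 124. From Randomization: 1:1 allocation. From Interim analyses and Primary analysis: final level 0.0471. A two-sided test is assumed, because only a two-sided calculation reproduces the stated totals.

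**Step 1: reproduce the plan's figures.** n per arm = 2 × (1.960 + 0.842)² × (SD/difference)².

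- Y: 71.2 per arm, 142.4 in total; with 71 per arm, 142.
- E: 54.2 per arm, 108.5 in total; with 54 per arm, 108.
- Multiplied by 1.15: 142 × 1.15 = 163.3 and 108 × 1.15 = 124.2, the stated 163 and 124.
- Divided by 0.85 instead: 142.4/0.85 = 167.6 and 108.5/0.85 = 127.6.

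Of the variants tried (rounding up per arm, t-based n, one-sided alpha, division by 0.85), only multiplication by 1.15 gives both stated integers. It also implies that the per-arm numbers were rounded down.

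**Step 2: patients left after 15% loss.** 163 × 0.85 = 138.6 against 142.4 needed. 124 × 0.85 = 105.4 against 108.5 needed. This comparison does not depend on which formula was used.

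**Step 3: power at 15% loss.** By normal approximation, power = Φ(δ − z), where δ = (difference/SD) × √n/2 and n is the total evaluable.

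- Y: δ = (7/14.91) × √138.55/2 = 2.763.
- E: δ = (10/18.59) × √105.4/2 = 2.761.
- z = 1.960 at 0.05 and 1.985 at 0.0471.

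| Two-sided level | Method | SHAFT-Y | SHAFT-E |
|---|---|---|---|
| 0.05 | normal | 78.9% | 78.9% |
| 0.05 | t-test | 78.3% | 78.1% |
| 0.0471 | normal | 78.2% | 78.1% |
| 0.0471 | t-test | 77.6% | 77.3% |

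Univariable regression on treatment is equivalent to the two-sample t-test, so the t-test rows fit the planned analysis more closely. The normal rows follow the approximation that reproduces the stated totals.

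**Step 4: separate the two causes (normal approximation).** Inflation and rounding: 80% to 78.9%, about 1.1 points. Level of 0.0471 in place of 0.05: about 0.7 points.

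**Step 5: do the interim looks return power?** The interim DASH test is one-sided against an improvement of 25 points, so it adds almost nothing at a true difference of 7 or 10. Had the looks tested a difference of zero at the stated levels, overall power would still be 78.9% (Y) and 78.8% (E).

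**Step 6: power at lower attrition, level 0.0471.**

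- At 5% loss: 82.0% (t-test) to 82.5% (normal) for Y; 81.8% to 82.5% for E.
- 80% power by normal approximation needs 145.0 and 110.5 evaluable: 1 − 145.0/163 = 11.0% and 1 − 110.5/124 = 10.9% attrition.
- By t-test, 80% is reached at 9.8% (Y) and 9.3% (E) attrition. Rounding up first to equal whole arms (148 and 114 in total) gives slightly lower percentages, which reflects the rounding only.

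**The case against.** The strongest reply is that the shortfall is too small to matter. By the normal approximation it is just under 2 points; by t-test it is 2.4 to 2.7 points. Under the same conditions the designs have 80% power for differences of about 7.2 and 10.2–10.3 instead of 7 and 10. An SD 2–3% below the assumed value would restore 80%, and both SDs come from age subsets of a single earlier trial. This stands, and it is why the point is minor. It does not make the printed statement correct.

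A second reply is that 15% is a cautious margin over the 5% seen in the source trial. This also stands. A reader might infer that neither trial can have 80% power, or that the design is materially underpowered. The documents do not support that: at 5% attrition power is about 82%, and the deficit appears only when attrition exceeds roughly 9–11%.

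A third reply is that lost patients are not wholly lost. The Primary analysis section plans multiple imputation from six covariates, and the Participant withdrawal section replaces patients who withdraw without baseline data. Any gain from imputation cannot be computed from the document, and the Sample size section claims none.

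Finally, an article may leave detail to a fuller plan. Here, however, the inputs, attrition, totals and final level are all printed, and they disagree.

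**Conclusion.** The statement is wrong as written, and the error is minor. At the plan's own 15% attrition and final level, power is about 77.6% (SHAFT-Y) and 77.3% (SHAFT-E) by t-test, or 78.2% and 78.1% by normal approximation, where the plan states 80%.

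This rests on three assumptions: the final test is two-sided, the plan's differences and SDs hold, and lost patients contribute no information. The multiplication by 1.15 is an inference from the matching totals, although the shortfall in evaluable patients holds without it. A one-sided final test at 0.0471 would give about 86%, but the stated totals do not fit a one-sided calculation.

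**What to change.** Keep 163 and 124 and correct the wording in Sample size in one of two ways:

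- state power as about 77–78% in each trial at 15% attrition and a two-sided level of 0.0471; or
- state that 80% power at 0.0471 holds up to about 9–10% attrition by t-test (about 11% by normal approximation), naming the method.

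In either case, print the attrition formula, the sidedness and the level used. The cost is wording only. The total of 287 stays the same wherever it appears, no further patients are needed, and the stated power becomes slightly less favourable.

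Recovering the power through a covariate-adjusted primary model is not part of this correction. The Primary analysis section fixes a univariable model and the Secondary analysis section holds the adjusted one, so the switch would change the primary analysis. It would also need covariates that explain about 6% of the DASH variance (0.058 in Y, 0.064 in E), an assumption for which the document gives no support.
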